## Abstract

**Background:**

The Health Enhancing Strength Training in Nonagenarians (STRONG) is a randomised control trial to assess the effectiveness of an aerobic and strength training program for improving muscle strength, functional capacity and quality of life in nonagenarians.

**Methods:**

Sixty (51 women) nonagenarians (age range: 90–102 years) who live in a geriatric nursing home will be randomly assigned to either a usual care (control) group (n = 30) or an intervention (training) group (n = 30). Participants allocated in the usual care group will receive general physical activity guidelines and participants allocated in the intervention group will also enrol in three weekly non-consecutive individualized training sessions (~45–50 min each) during 8 weeks. The exercise program will consist of muscular strength [with a special focus on leg press at 30% (start of the program) to 70% 1 repetition maximum (end)] and aerobic exercises (cycle-ergometry during 3–5 to 15 minutes at 12–14 points in the rate of perceived exertion scale).

**Results:**

Results from STRONG will help to better understand the potential of regular physical activity for improving the well-being of the oldest population groups.

**Conclusion:**

The increase in life expectancy together with the dramatic decrease in birth rates in industrialized countries calls the attention to health care systems and public health policymakers to focus attention on promoting healthy lifestyle in the highest sector of the population pyramid. Our study attempts to improve functional capacity and QOL of nonagenarians by implementing an individualised aerobic and strength training program in a geriatric residential care. Results from STRONG will help to better understand the potential of regular physical activity for improving the well being even in persons aged 90 years or over.

**Trail Registration:**

ClinicalTrials.gov ID: NCT00848978

## Background

The fact that in western societies people are living longer is demanding the exploration of new roads to promote healthy ageing instead of merely treating the diseases of old age [1]. A powerful intervention for both promoting healthy ageing and treating age-related disorders is regular physical activity (PA). The American College of Sports Medicine (ACSM) and the American Heart Association (AHA) recently launched the PA recommendations for older adults (≥ 65 years): this population group should enrol in aerobic and strength activities most days of the week [2].

Maintenance of adequate muscle mass and strength plays a key role in the prevention of numerous chronic diseases and in the ability to cope with activities of daily living (ADLs) [3,4]. Resistance (strength) exercise training increases muscle mass and strength [5,6], and is currently recommended by the major health organizations for improving health and fitness [6-10]. In elderly people, functional capacity becomes more directly dependent on muscular fitness as these persons also experience age-associated declines in muscle mass (i.e. sarcopenia) and thus in muscular strength. Sarcopenia contributes to the decreased capacity for independent living and reduced ability to cope with ADLs and thus increases the burden for the caregiver and community [11]. Already in the 80s, Bortz [12] indicated that many biological changes that are commonly attributed to ageing, e.g. sarcopenia, can be reverted, since they are mostly caused by disuse.

Several prospective studies indicated that cardiorespiratory fitness and muscular strength are inversely associated with all-cause mortality [13-32]. A recent meta-analysis located 66 randomised trials on resistance exercise training interventions for older adults (mean age of 60 years and over); it was concluded that progressive strength training is effective to increase muscular strength in this subpopulation [33]. Though strength training is also effective in the eldest (86–96 years) [34], whether this intervention does also improve the functional capacity, quality of life (QOL) and ability to perform ADLs in nonagenarians (≥ 90 years) remains to be elucidated. Intervention studies examining with nonagenarians are scarce owing to the difficult access to such particular population. According to the United Nations (average for the 2005–2010 period), Spain is the sixth country in the world with the longest life expectancy at birth [35]. Therefore, especially in our country, it is of public health and clinical relevance to better understand the effects of regular PA in very old people (≥ 90 years).

### Objectives

The primary objectives of the Health Enhancing Strength Training in Nonagenarians (STRONG) trial is to assess the effectiveness of an 8-week aerobic and strength training program for improving muscle strength, daily functional capacity and quality of life (QOL) in nonagenarians. Primary outcomes were measures of muscular strength, daily physical functioning (Tinetti scale, Barthel index, ambulation ability), and QOL and well-being. We hypothesise that an individualised training program (intervention) focusing on strength exercises and delivered to nonagenarians by specialists in exercise training and health educators in a geriatric nursing home will result in a improvement in the aforementioned outcomes compared to the usual care. A secondary objective is to assess the effects of the intervention on PA levels and body composition. As such, measures of these two variables were secondary outcomes.

## Methods/Design

### Study design

The present study is a randomised controlled trial (RCT). The Medical Ethics Committee of *Hospital General Universitario Gregorio Marañón *(Madrid, Spain) approved the study design, study protocols and informed consent procedure. All participants have to provide a written informed consent. After baseline measurements, they will be randomly allocated to the control or intervention group. The participants will be followed for 8 weeks. All follow-up examinations will be performed in the same setting (geriatric nursing home, *Los Nogales-Pacífico*, Madrid, Spain) and by the same investigators as in the baseline measurements. The study will be performed between March 2009 and September 2009, following the ethical guidelines of the Declaration of Helsinki, last modified in 2000.

### Study participants and selection criteria

STRONG participants include 60 community-dwelling elderly people aged 90 years or over recruited from a geriatric nursing home (Los Nogales-Pacífico, Madrid, Spain). All participants received a comprehensive medical examination.

The inclusion criteria for STRONG are:

- Age: 90 years or over.

- Planning to stay in the same nursing home during the study.

- Able to ambulate, with or without assistance.

- Able to communicate.

- Informed consent: Must be capable and willing to provide consent.

The exclusion criteria for STRONG are:

- Acute or terminal illness.

- Myocardial infarction in the past 3 months.

- Not capable to ambulate.

- Unstable cardiovascular disease or other medical condition.

- Upper or lower extremity fracture in the past 3 months.

- Severe dementia.

- Unwillingness to either complete the study requirements or to be randomised into control or training group.

- Presence of neuromuscular disease or drugs affecting neuromuscular function.

Figure 1 illustrates the participant flow from recruitment to randomisation.

**Figure 1 F1:**
[figure not shown]
**Flow diagram of the study participants**.

### Randomisation and blinding

Participants will be randomly assigned to either the control or training group with a block on gender and ambulation ability based on the Functional Ambulation Classification (FAC) scale (score 0–3 *vs *4–5) [36] by the data manager based on a computer-generated randomisation sequence. The group assignment coding (0 for usual care and 1 for intervention) will be concealed to the research group. The assessment staff will be blinded to participant randomisation assignment. Participants will be explicitly informed and reminded to not to discuss their randomisation assignment with assessment staff. It will not be possible to conceal the group assignment from the staff involved in the training.

### Sample size and statistical power

The required sample size was determined for one of the primary outcome variables, i.e. functional capacity using the Tinetti scale [37]. We believe that a clinically relevant change is a ≥ 30% increase in the aforementioned scale. We expect the control group to improve ~0 to 5%; thus, we can detect differences of at least ≥ 35% with a power > 80% and an α of 0.05 with two groups of 25 subjects. Assuming a maximum loss of follow-up of 20%, we will recruit a total of 60 nonagenarians. We will be also able to detect a significant difference of 4 points in the Tinetti scale with this number of participants, assuming a standard deviation of 5 points.

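### Recruiting 60 does not keep 25 per group after a 20% loss: 24 per group remain, and 60 covers a loss of at most 16.7% (wrong as written, minor)

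*Protocol article*

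**What the plan says.** All the relevant figures but one are in the protocol article, section Sample size and statistical power.

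- The main claim is about a percentage difference on the Tinetti scale: "We expect the control group to improve ~0 to 5%; thus, we can detect differences of at least ≥ 35" per cent, "with a power > 80% and an α of 0.05 with two groups of 25 subjects". The requirement is therefore 25 per group, 50 in total.
- The allowance for attrition follows: "Assuming a maximum loss of follow-up of 20%, we will recruit a total of 60 nonagenarians".
- A second claim comes after that. The trial is also said to be able to "detect a significant difference of 4 points in the Tinetti scale with this number of participants, assuming a standard deviation of 5 points". No power is given in this sentence.

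The Methods paragraph of the abstract gives the split of the 60: "usual care (control) group (n = 30) or an intervention (training) group (n = 30").

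**The concern.** The number to recruit should be large enough that, after the largest loss the plan assumes, the required number is still under observation. Here it is not: at 20% loss, 30 per group become 24, one fewer than the 25 on which the power claim rests. The total of 60 is what results from adding 20% to 50. Allowing for a 20% loss among those recruited means dividing 50 by 0.8.

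At stake is whether the stated combination of 25 per group, 20% loss and 60 recruits can be relied on, and how much power is left at the loss the plan says it can absorb. Any deficit matters more if 25 per group has no margin. It has almost none for the 4-point difference with SD 5, the only target that can be recalculated.

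**Working it through.** **Inputs.** From the sample-size section: 25 per group, maximum loss 20%, 60 recruited, α = 0.05, a difference of 4 points, SD 5. From the abstract: 30 per group. Assumption: a two-sided test, since the section does not state sidedness.

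**Step 1. Reproduce the 25 per group.** Using the normal approximation for two means with 80% power:

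n per group = 2 × (1.960 + 0.842)² / (4/5)² = 24.5, rounded up to 25.

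So 4 points with SD 5 reproduces 25 exactly. A one-sided test would need only 20 per group, which does not explain the stated 25.

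**Step 2. Reproduce the 60.**

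- Division by the retained fraction: 50 / (1 − 0.20) = 62.5, so 63 in total. By arm, 25 / 0.8 = 31.25, so 32 per arm and 64 in total.
- Multiplication by one plus the loss: 50 × 1.20 = 60.

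Only the second gives the stated total.

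**Step 3. What 60 delivers.**

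- At 20% loss: 60 × 0.8 = 48, or 24 per group.
- Largest loss that still leaves 50: 1 − 50/60 = 16.7%.
- Shortfall at 20% loss: 50 − 48 = 2 participants under observation, equivalent to 3 or 4 recruits (63 − 60 or 64 − 60).

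**Step 4. Power for 4 points, SD 5, two-sided α = 0.05.** The standardised difference is 4/5 = 0.8. The noncentrality is 0.8 × √(n/2), which is 2.771 at n = 24 and 2.828 at n = 25. The normal approximation takes Φ(noncentrality − 1.960); the t test uses the noncentral t distribution with 2n − 2 degrees of freedom.

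| Per group | Normal approximation | t test |
|---|---|---|
| 24 (60 recruited, 20% lost) | 79.1% | 77.4% |
| 25 (stated requirement) | 80.7% | 79.1% |
| 30 (no loss) | 87.3% | 86.1% |

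Under the normal approximation, 25 is the smallest group size that reaches 80%, and 24 falls just below it. Under the t test, 25 is already slightly short before any loss. Going from 25 to 24 costs 80.7 − 79.1 = 1.6 points by the first method and 79.1 − 77.4 = 1.7 points by the second.

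**Step 5. The 35% difference.** Its power cannot be calculated, because the section gives neither a baseline mean nor an SD on the percentage scale. To show the range, assume that SD 5 applies and that the difference is 35% of the baseline mean. With 24 per group and a t test, baseline means of 10, 12, 14 and 16 points give power of 66%, 81%, 91% and 97%. The 80% line is crossed at a difference of about 4.13 points, a baseline mean of 4.13/0.35 = 11.8 out of 28. These baselines are illustrations, not figures from the article.

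**The case against.** The strongest counter-argument concerns power. A reader might infer that the plan as a whole falls below 80% power because of the attrition figure. The article does not support that, for three reasons.

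- The claim of more than 80% is attached to the 35% difference, whose power cannot be checked. Step 5 shows that it could lie on either side of 80%.
- The 4-point sentence carries no stated power. Its reference to the number of participants comes straight after the 60, so it may mean 30 per group, where power is about 86% by t test. That 4 points with SD 5 gives 25 per group makes a link to the main claim plausible, but it remains an inference.
- By t test, 25 per group gives 79.1% before anyone is lost. Under that method the attrition figure deepens a small existing shortfall and does not create it.

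A reader might also take it as established that 50 was multiplied by 1.2. The arithmetic fits, but the article shows no formula.

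Other points bear on weight. Twenty per cent is given as a maximum, so 24 per group is the worst case allowed for. The Discussion reports 58 eligible residents and 48 who had consented by April 2009, so the choice between 60 and 63 or 64 had little practical consequence by then. The Statistical analysis section plans multiple imputation and a repeated-measures analysis, so actual power is not simply that of a t test on 48 people. However, the stated calculation uses neither, and imputation does not turn 48 people with follow-up into 50.

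All of this limits the consequence and none of it removes the miscount. Nor does the brevity of an article explain it: nothing is missing here, since the three figures are printed together and disagree.

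**Conclusion.** Wrong as written, and minor. The statement that 60 recruits cover a 20% loss while 25 per group are needed is incorrect: 24 per group remain, and 60 covers at most 16.7%. This follows from the article's own figures and needs no assumption beyond reading the loss as a share of those recruited.

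The deficit is one participant per group, or 3 to 4 recruits. For 4 points with SD 5 and an assumed two-sided α of 0.05, the miscount costs under two points of power. Normal-approximation power goes from just above 80% to just below it; t-test power starts just below 80% and falls a little further. No conclusion can be drawn about power for the 35% difference. The point does not call the design or the planned analysis into question.

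**What to change.** Keep 60 and correct the sentence on attrition in one of two ways:

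- *Recruiting 60 allows for up to 16.7% loss to follow-up while keeping 25 per group*; or
- *With 20% loss, 24 per group remain, giving about 79% (normal approximation) or 77% (t test) power for a difference of 4 points with SD 5*.

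Whichever is chosen, name the method behind any power figure, and say whether the 4-point statement refers to 24, 25 or 30 per group.

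The cost is one or two sentences. The stated allowance becomes slightly less favourable. Enrolment, design and analysis do not change.

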### Statistical analysis

For group comparisons at baseline (usual care *vs *intervention), we will analyse continuous variables with a Student's *t *test (or its non-parametric equivalent) for unpaired data, and Chi-square tests for nominal data. We will adjust multiple comparisons for mass significance [38,39]. We will also examine the differences between drop-outs and participants who remained in the study. We will analyse the data according to the intention-to-treat principle [40]. We will handle missing data due to drop-outs or non-compliance using multiple imputation methods. To fully appreciate the potential influence of missing responses, we will perform sensitivity analysis.

We will use a two-factor (group and time) analysis of variance (ANOVA) with repeated measures to assess the training effects on the primary outcomes [muscular strength, daily physical functioning (Tinetti scale, Barthel index, ambulation ability) and QOL and well-being] and secondary study outcomes (anthropometry and PA levels). For each outcome variable we will report the effect size and the level of significance corresponding to the main group (between-subjects), time (within-subjects) and interaction (group × time) effects. In order to prevent type I error, we will perform post hoc comparisons (pre *vs *post by group) only when a significant interaction effect is present. The level of significance will be set to = 0.05.

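### The planned group × time ANOVA is valid, but it uses baseline less efficiently than ANCOVA, omits the randomisation factors and does not name the treatment effect

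*Protocol article*

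**What the plan says.** Randomisation is done "with a block on gender and ambulation ability based on the Functional Ambulation Classification (FAC) scale", with FAC split at 0–3 vs 4–5 (Randomisation and blinding).

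The Statistical analysis section then fixes the model: "We will use a two-factor (group and time) analysis of variance (ANOVA) with repeated measures to assess the training effects on the primary outcomes". The same sentence extends it to the secondary outcomes. For each outcome the plan will give an effect size and a significance level for the "main group (between-subjects), time (within-subjects) and interaction (group × time) effects". It does not say which of the three is the treatment effect. Pre-to-post comparisons within each group follow only if the interaction is significant. Analysis is by intention to treat, with multiple imputation for missing data.

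The trial is sized "with a power > 80% and an α of 0.05 with two groups of 25 subjects". The Sample size section also claims that a Tinetti difference of 4 points can be detected, and for this it works "assuming a standard deviation of 5 points".

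**The concern.** Three features of the stated model deserve attention.

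- **Baseline enters only through change.** The article describes baseline measurement, 8 weeks of follow-up and pre-versus-post comparisons. I read this as one pre and one post value per person. The group × time F test is then the same test as a t test on change scores. It subtracts the whole baseline value, whatever its correlation with the outcome, and so leaves part of any chance baseline imbalance in the estimate.
- **The randomisation factors are absent.** Gender and FAC group restrict the allocation but do not appear in the analysis.
- **Three effects are reported and none is named.** The group main effect averages in a value taken before treatment. The time effect does not compare randomised arms.

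At stake is precision in a small trial, and a reader's ability to tell which p-value answers the trial's question.

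**Working it through.** **Inputs.** From the Sample size section: difference 4 Tinetti points, SD 5, α 0.05, 25 evaluable per arm. Two-sided testing is my assumption; one-sided would need only 20 per arm. The pre–post correlation r is not in the article and is varied. The article does not say whether SD 5 belongs to the score or to the change, so both readings are shown.

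**The plan's own figure.** n per arm = 2 × (1.96 + 0.84)² × 5² / 4² ≈ 24.5, rounded up to 25. Power at 25 per arm is 0.807 by the normal approximation and 0.791 by the noncentral t. The figure reproduces, with little to spare.

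**Variance per person, equal SD at both visits.**

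- Change score (the interaction test): 2(1 − r)SD²
- ANCOVA on the 8-week value: (1 − r²)SD²
- Ratio: (1 − r²) / [2(1 − r)] = (1 + r)/2

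**Power for 4 points, SD 5 read as the SD of the score.** Noncentral t; ANCOVA has 45 residual df (50 − 5) and the interaction test 48. The n column uses the normal approximation for 80% power.

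| r | SD of change | ANCOVA residual SD | Variance ratio | Power, interaction | Power, ANCOVA | n per arm, interaction vs ANCOVA |
|---|---|---|---|---|---|---|
| 0.3 | 5.92 | 4.77 | 0.65 | 0.65 | 0.83 | 35 vs 23 |
| 0.5 | 5.00 | 4.33 | 0.75 | 0.79 | 0.89 | 25 vs 19 |
| 0.7 | 3.87 | 3.57 | 0.85 | 0.95 | 0.97 | 15 vs 13 |
| 0.8 | 3.16 | 3.00 | 0.90 | 0.992 | 0.996 | 10 vs 9 |

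A simulation at r = 0.5, 0.7 and 0.8 agreed to within about one percentage point. The two further df for the stratum terms change power by about 0.001.

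**SD 5 read as the SD of change.** The interaction test has power 0.79 whatever r is. ANCOVA has 0.89, 0.85, 0.83 and 0.81 at r = 0.5, 0.7, 0.8 and 0.9.

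**Where the lost precision sits.** Given an observed baseline difference d, the change-score contrast is shifted by −(1 − r)d. With 25 per arm and a score SD of 5, one standard error of d is 5√(2/25) = 1.41 points. At r = 0.5 that moves the estimate by 0.71 points, about 18% of the 4-point target. The shift averages to zero over randomisations, so it is not bias. Its variance is the excess in the table: 2(1 − r) − (1 − r²) = (1 − r)².

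**Group main effect.** It compares person means over the two visits, so its expected size is (0 + 4)/2 = 2 points, with SD 5√((1 + r)/2). Power is 0.41, 0.36, 0.32 and 0.31 at r = 0.3, 0.5, 0.7 and 0.8.

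**Time main effect.** With no treatment effect and an assumed 1-point drift in both arms, it was significant in 27% of simulated trials at r = 0.5 and 87% at r = 0.9. The interaction and ANCOVA tests both stayed near 5%.

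**The case against.** The strongest reply is that the plan already contains a valid test. The interaction is unbiased for the randomised effect, holds its type I error, and is the gate for every later comparison. This stands. A reader might infer that the plan will take main effects or within-arm tests as evidence of benefit. The article does not say so, and the within-arm tests cannot be reached without a significant interaction. The low power of the group main effect therefore does not describe the power of the trial's treatment test.

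Second, the gain depends on an r that nobody has stated. Three familiarisation sessions, the same investigators and setting at both visits, and only 8 weeks between them make a high correlation plausible, though not shown. If SD 5 is the SD of change, the interaction test delivers about what the sample size section intended. This also stands: the calculation does not show the trial to be underpowered.

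Third, differences in level between strata cancel in a change score. Leaving gender and FAC out costs precision only if they predict change, and omission does not bias the estimate. It usually makes the test conservative when they do. No figure in the article lets the stratum gain be sized, so none is claimed.

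Fourth, it is tempting to rework the power at 12 and 18 participants, the counts in the Discussion. Those are a snapshot from April 2009, with the study still under way. The design is 25 evaluable per arm.

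Finally, a journal article may leave covariates to an analysis plan. That would answer silence, but here a two-factor model is stated.

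**Conclusion.** The point holds as one of efficiency and clarity, not of validity. The stated model is sound for the treatment effect through its interaction, but it is never more precise than ANCOVA apart from a trivial loss of df, and it ignores covariates the trial already holds.

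With SD 5 as the score SD, the gain is about 18 percentage points of power at r = 0.3, 10 at r = 0.5, 2 to 3 at r = 0.7, and negligible from 0.8. With SD 5 as the SD of change, it runs from about 10 points at r = 0.5 to 2 at r = 0.9. These figures assume equal SDs at both visits, one pre and one post value, and two-sided testing at 0.05.

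Separately, and whatever r is, the plan should say which effect answers the question. Two of the three it reports do not directly estimate training against usual care: the group main effect has half the expected size, and the time effect is not a randomised comparison.

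**What to change.** For each continuous or score outcome, name one treatment effect: the between-arm difference at 8 weeks from an ANCOVA with group, the outcome's baseline value, gender and FAC stratum (0–3 vs 4–5). Enter gender and FAC as main effects only. With 60 − 51 = 9 men planned, a full cross-classification would leave very small cells.

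Report this difference with its 95% CI for every outcome, significant or not, and use the same model within the multiple imputation. Label the group and time main effects, and the within-arm tests that follow a significant interaction, as descriptive.

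The cost is a change of wording and three model degrees of freedom, with a negligible effect on power. Baseline values, gender and FAC group are already recorded, so no new data are needed.
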